# Protocol paper: a multi-center, double-blinded, randomized, 6-month, placebo-controlled study followed by 12-month open label extension to evaluate the safety and efficacy of Saracatinib in Fibrodysplasia Ossificans Progressiva (STOPFOP)

**DOI:** 10.1186/s12891-022-05471-x

**Published:** 2022-06-01

**Keywords:** Fibrodysplasia Ossificans Progressiva, Saracatinib, AZD0530, Clinical trial, Drug repurposing, Drug repositioning

## Abstract

**Background:**

Fibrodysplasia Ossificans Progressiva (FOP) is a genetic, progressive and devastating disease characterized by severe heterotopic ossification (HO), loss of mobility and early death. There are no FDA approved medications. The STOPFOP team identified AZD0530 (saracatinib) as a potent inhibitor of the ALK2/*ACVR1*-kinase which is the causative gene for this rare bone disease. AZD0530 was proven to prevent HO formation in FOP mouse models. The STOPFOP trial investigates the repositioning of AZD0530, originally developed for ovarian cancer treatment, to treat patients with FOP.

**Methods:**

The STOPFOP trial is a phase 2a study. It is designed as a European, multicentre, 6-month double blind randomized controlled trial of AZD0530 versus placebo, followed by a 12-month trial comparing open-label extended AZD0530 treatment with natural history data as a control. Enrollment will include 20 FOP patients, aged 18–65 years, with the classic FOP mutation (ALK2 R206H). The primary endpoint is objective change in heterotopic bone volume measured by low-dose whole-body computer tomography (CT) in the RCT phase. Secondary endpoints include ^18^F NaF PET activity and patient reported outcome measures.

**Discussion:**

Clinical trials in rare diseases with limited study populations pose unique challenges. An ideal solution for limiting risks in early clinical studies is drug repositioning – using existing clinical molecules for new disease indications. Using existing assets may also allow a more fluid transition into clinical practice.

With positive study outcome, AZD0530 may provide a therapy for FOP that can be rapidly progressed due to the availability of existing safety data from 28 registered clinical trials with AZD0530 involving over 600 patients.

**Trial registration:**

EudraCT, 2019–003324-20. Registered 16 October 2019, https://www.clinicaltrialsregister.eu/ctr-search/trial/2019-003324-20/NL. Clinicaltrials.gov, NCT04307953. Registered 13 March 2020.

**Supplementary Information:**

The online version contains supplementary material available at 10.1186/s12891-022-05471-x.

## Background

Rare diseases are defined in Europe as disease with a prevalence of less than 1 in 2000. There are more than 7000 rare diseases, cumulatively affecting the lives of an estimated 3.5–5.9% of the global population [1]. Together, rare diseases provide a significant medical, psychological and economic burden, while posing unique and urgent challenges for research and drug development [2, 3].

An especially devastating rare disease is Fibrodysplasia Ossificans Progressiva (FOP): this genetic, disease is characterized by severe heterotopic ossifications (HO) in muscle, tendons and ligaments and has a prevalence of about 1 in 1 million [4, 5]. HO is often, but not always, preceded by inflammatory symptoms (e.g. swelling, pain and redness) which is known as a flare-up [6, 7]. Culminating heterotopic bone results in progressive immobility and morbidity, ultimately leading to a reduction in lifespan to a median of 56 years [8]. FOP is caused by an autosomal dominant germline mutation in the gene *ACVR1* encoding the BMP receptor kinase ALK2), with an overwhelming majority of patients (97%) exhibiting the ‘classical’ gain of function mutation R206H (c.617G > A) [9]. This mutation leads to aberrant signaling in response to activin A, as well as hypersensitivity to BMP ligands culminating in HO [10, 11].

Only an estimated 5% of rare diseases have a form of FDA approved treatment [12]. Unfortunately, FOP is not one of them. The high costs associated with drug development can hinder development of novel therapies, and therefore repositioning of existing drugs becomes an alluring option for treatment of rare diseases. Toxicology reports, pharmaceutical dossiers and clinical safety data have often already been established for these drugs which may significantly reduce development costs and time to market approval [13, 14].

Kinases have emerged as an important therapeutic target in multiple diseases. This has led to the development of a plethora of approved and/or clinically tested small molecule kinase inhibitors [15, 16]. Such a drug repertoire holds promise that some clinical inhibitors might also inhibit ALK2 in FOP, which has been demonstrated for preclinical kinase inhibitors by experiments in FOP mouse models [17, 18]. Williams et al. performed an unbiased screen on clinically tested small-molecule inhibitors which revealed that saracatinib (AZD0530) had low nanomolar binding affinity for ALK2 and could prevent HO in two FOP mouse models [19].

These findings convinced our team that saracatinib (AZD0530) has favourable characteristics as an investigational drug for FOP. If proven to be safe in patients with FOP and effective in preventing the formation of heterotopic ossification, AZD0530 might represent a rapidly translatable therapy for FOP, with the significant advantage of extensive safety data from over 28 registered clinical trials involving over 600 patients available [19]. The Saracatinib trial TO Prevent Fibrodysplasia Ossificans Progressiva (STOPFOP) is an investigator-initiated trial that aims to investigate both the effectiveness and the safety of AZD0530 for use in patients with FOP [20].

## Methods / design

### Study design

This phase 2a study is designed as a European multicentre 6-month double blind randomized controlled trial (RCT) of AZD0530 versus placebo, followed by a 12 month open-label extension phase.

Eligible subjects are randomized 1:1 to one of two groups: Group 1 will undergo treatment with 100 mg AZD0530 once daily for the entire duration of the trial; group 2 will first be given placebo for the first 6 months before starting AZD0530 for 12 months. After undergoing baseline evaluation, the main outcome criteria and safety endpoints are evaluated at 6, 12 and 18 months after first study drug dosing. In addition, participants are evaluated on safety endpoints 3 weeks after first drug dose/switch to open label phase and after 3, 9 and 15 months. There will be three comparison groups: AZD0530 versus placebo in the 6-month RCT phase (A), placebo group (months 1–6) versus the open label extension phase of the same group (months 7–12) (B) and Open label extension group versus age-, gender-, and demographically-matched historic controls (C).

Figure 1a summarizes the study design and study procedures, Fig. 1b illustrates the comparison groups.

**Fig. 1 Fig1:**
[figure not shown]
Study overview (**A**) and comparison groups (**B**). IFOPA = International Fibrodysplasia Ossificans. Association, PET = Positrion Emission Tomography, CT = Computer Tomography, ROM = Range Of Motion

This study included the first patient in August 2020 and will continue for 18 months after inclusion of the final study participant. Protocol version at time of writing is 12.2. For a completed SPIRIT checklist, see the Additional file 2.

### Participants

Male and female adult (18 years or older) patients with a confirmed diagnosis of FOP caused by the *ACVR1*^R206H/+^ genomic sequence will be eligible for the study. Participants are required to understand and undergo all study procedures. Finally, participants must adhere to effective contraceptive methods throughout the duration of participation in the study.

The exclusion criteria are focused on increasing safety for participants in the study and minimizing risks associated with participation in a clinical study. They include: pregnancy, significant concomitant illness or uncontrolled other illnesses, active bleeding or risk thereof, serious impairment of renal or liver function, and known allergy to any components of the AZD0530 or placebo tablets. Participants cannot simultaneously participate in other interventional trials or studies that use imaging procedures. A full list of patient eligibility criteria can be found in the Additional file 1.

### Recruitment and screening

Recruitment will be performed by dedicated FOP physicians at three of the main FOP centers in Europe: Amsterdam University Medical Centers in The Netherlands, Klinikum Garmisch-Partenkirchen in Germany and Royal National Orthopaedic Hospital in the United Kingdom. Furthermore, patients will be made aware of the trial through national and international FOP patient organisations that are represented in the Stakeholders Board of the study, presentations on patient symposia/webinars and through social media.

At least 1 week prior to the screening visit, patients will receive a full package of study information. After obtaining consent, the patient will be screened for eligibility on site.

#### Randomisation, allocation and (un)blinding

Participants will be randomly assigned to either AZD0530 or placebo group by the clinical trials pharmacy of the Amsterdam UMC. Randomisation will be stratified according to site and performed in blocks of two using a random number table. Patients and study team members will remain blinded until the analysis of study data is completed.

Emergency unblinding can only occur in exceptional circumstances mentioned in Additional file 1.

### Intervention, comparator and concomitant care

Dependent on allocation group, patients will take AZD0530 100 mg once daily or matched placebo orally during 6 months, immediately followed by an open-label extension in which all patients will receive AZD0530 100 mg once daily oral dose for a further 12 months. The placebo is not discernible from the study drug. A placebo comparator was chosen because no FDA/EMA approved drug currently exists for the indication FOP.

#### Discontinuation of study drug

Treatment with study drug will be discontinued by the investigator if a life-threatening AE or a serious adverse event (SAE) occurs; if a pregnancy is confirmed; if the study is closed by the sponsor or regulatory authorities, or if the patient wishes to stop. An elevation of the concentrations of aspartate/alanine transaminase (AST/ALT) of more than five times the upper limit of normal (or three times if there are further signs of severe liver damage) is also a ground for discontinuation. Finally, the drug will be temporarily discontinued if symptomatic SARS-CoV-2 infection occurs, until resolution of symptoms.

#### Adherence

Participants are reminded to take the study drug at the end of the daily diary and at each study visit. Drug adherence will be monitored through pill count at each visit after starting medication. Furthermore, levels of AZD0530 will be monitored at visits 5, 8 and 10.

#### Concomitant care

During the trial, and 2 weeks after the final dose, participants are not allowed to take other drugs that might affect bone turn-over (e.g. bisphosphonates), other experimental drugs, cancer treatments or drugs that cause greater than threefold change in AZD0530 exposure through CYP3A4 interaction.

Escape medication (prednisone and NSAIDs) for exacerbation of FOP is allowed in line with the current FOP guidelines [21].

### Participant timeline

Table 1 shows the schedule of enrollment, intervention, and assessments during the STOPFOP study in accordance with the SPIRIT statement [22]. The flow diagram of the study is shown in Fig. 1a.

**Table 1 Tab1:**
[figure not shown]
Schedule of enrollment, intervention, and assessments during study

*RCT* Randomized controlled trial, *CAJIS* Cumulative analogue joint involvement scale, *SF-36* 36-item Short Form Survey, *FOP I-ADL* Fibrodysplasia Ossificans Progressiva Instrumental Activities of Daily Living.

*Telephone/virtual visit unless clinically indicated. ^†^Includes pregnancy test for women of childbearing potential. ^‡^No more than 7 days between baseline PET/CT and start study medication

### Endpoints

#### Primary endpoint

The primary endpoint is the change in heterotopic bone volume between baseline and 6-month follow-up as measured by low-dose whole body CT. This difference will be compared between the AZD0530 group and the group that received placebo (comparison group A).

#### Secondary endpoints

Secondary endpoints can be divided into several categories:Adverse events: The incidence and severity of adverse events during the different stages of the trial.Imaging endpoints including the change in HO volume and FOP activity on ^18^F NaF PET/CT.Clinical endpoints such as the number of reported flare-ups through daily diary, cumulative analogue joint involvement scale (CAJIS), Range of Motion, and questionnaires Short Form Health Survey-36 (SF-36) and FOP Independent Activity of Daily Living (FOP-IADL).Markers target engagement and efficacy surrogates including bone turn-over biomarkers, AZD0530 pharmacokinetic measurements, and experimental markers.

The outcomes are compared in all three comparison groups.

The endpoints are in line with the agreed Core Outcome Sets by the International Clinical Council on FOP [23]. A detailed description of the endpoints can be found in Additional file 1.

### Data management and data safety monitoring

Data will be handled confidentially. A subject identification code list will be used to link the data to the subject. The handling of personal data will comply with the EU General Data Protection Regulation and any local regulations. Research data will be stored for a period of 20 years.

To review safety and efficacy outcomes during the trial, an independent Data Safety Monitoring Committee (DSMB) will be assembled. The DSMB will consists of independent expert and will include a statistician. The DSMB will primarily monitor safety endpoints, but may recommend also termination of modification of the study in case of interim efficacy of over 75% on the primary endpoint.

Project data will be made publically anonymously available either via the consortium website or via public databases.

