### Statistical approach

#### Sample size calculations

Based on the Natural History Study of FOP, progression of HO in FOP is estimated at 120,000 mm^3^ on average per 6-month period with a standard deviation of 48,000 mm^3^ [24]. Expert consensus defines a meaningful decrease in the rate of HO progression as at least 50% reduction in treated vs. control patients, or 60,000 mm3, with a standard deviation of 24,000 mm^3^. Using this projected impact, using a t-test with two-sided alternative, with unequal variances, a trial with treatment and placebo arms of *n* = 8 each would be 80% powered to detect this minimum clinically meaningful difference with an α = 0.05 during the initial 6-month study.

Taking into account an expected drop-out rate of 20%, we calculated the necessary number of participants to be 20 at the start of the study.

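### The DSMB's 75% efficacy trigger is a bare point estimate: it is tied to no significance boundary, minimum number of scans or alpha allocation

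*Protocol article*

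**What the plan says.** In the protocol article, Data management and data safety monitoring, the committee's main remit is safety: "The DSMB will primarily monitor safety endpoints". The same sentence adds an efficacy role: it "may recommend also termination of modification of the study in case of interim efficacy of over 75% on the primary endpoint" (read here as termination or modification). The committee is independent and includes a statistician.

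The quantity monitored is defined under Primary endpoint: "The primary endpoint is the change in heterotopic bone volume between baseline and 6-month follow-up as measured by low-dose whole body CT", compared between AZD0530 and placebo.

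Sample size calculations takes HO progression as "estimated at 120,000 mm^3^ on average per 6-month period with a standard deviation of 48,000 mm^3" and the target as "at least 50% reduction in treated vs. control patients, or 60,000 mm3, with a standard deviation of 24,000 mm^3". The method is stated as "using a t-test with two-sided alternative, with unequal variances", with "arms of *n* = 8 each would be 80% powered to detect this minimum clinically meaningful difference with an α = 0.05". The full 0.05 goes to that comparison. Analyses of primary endpoint allows a t-test or, for non-normal data, a Mann-Whitney test.

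**The concern.** The article does more than announce that efficacy will be monitored. It fixes the criterion, and the criterion is a percentage alone. An observed percentage reduction from a few patients per arm carries very different weight depending on how variable the outcome is and how many scans lie behind it, and the rule refers to neither.

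The stake is the randomised comparison itself: about 20 people over 6 months. Comparison B (the placebo group before and after switching) and comparison C (historic controls) are not randomised, so a comparison cut short cannot be replaced from elsewhere in the trial. A trial stopped because its estimate passed 75% would also report an estimate selected for being large.

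**Working it through.** **Inputs from Sample size calculations.** Placebo mean 120,000 mm³ per 6 months, SD 48,000; treated mean under the target effect 60,000, SD 24,000; two-sided α = 0.05; 8 per arm. The planning CV is 48,000/120,000 = 40%.

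**Assumptions.** Efficacy is read as the relative reduction in mean HO change. With no drug effect, both arms have the same mean and SD. Interim numbers per arm are illustrative, because the article gives none.

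**1. The plan's own figure.** SE = √((48,000² + 24,000²)/8) = 18,974; noncentrality = 60,000/18,974 = 3.16; Satterthwaite df = 10.3. Power is 81.5%, so the stated 80% at 8 per arm reproduces. Also 16/0.8 = 20 participants.

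**2. False crossing at the plan's SD.** The trigger is treated mean < 0.25 × placebo mean, an expected gap of 0.75 × 120,000 = 90,000 mm³, or 90,000/48,000 = 1.9 SDs. With no effect,

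P(cross) = Φ(−90,000 / (48,000 × √(1.0625/n))), where 1.0625 = 1 + 0.25².

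| n per arm | P(cross), no effect |
|---|---|
| 2 | 0.50% |
| 3 | 0.08% |
| 4 | 0.014% |
| 5 | 0.002% |

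Looking after every pair from 2 to 7 per arm gives 0.5% in total (simulation, 300,000 runs). Overall type I error (trigger, or final Welch test at 8 per arm) moves from 4.8% to 5.3%.

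**3. Is meeting the trigger evidence?** Take an observed difference of exactly 90,000 with observed SDs of 48,000 and 24,000. Then t = 90,000/√((48,000² + 24,000²)/n), with Satterthwaite df. The last column is the smallest two-sided p that an exact Mann-Whitney test can give, 2/C(2n, n).

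| n per arm | t | df | Welch p | Mann-Whitney minimum p |
|---|---|---|---|---|
| 2 | 2.37 | 1.5 | 0.18 | 2/6 = 0.33 |
| 3 | 2.90 | 2.9 | 0.064 | 2/20 = 0.10 |
| 4 | 3.35 | 4.4 | 0.025 | 2/70 = 0.029 |
| 5 | 3.75 | 5.9 | 0.010 | 2/252 = 0.0079 |

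At 2–3 per arm the trigger can be met without nominal significance. If the data call for Mann-Whitney, that test cannot reach 5% at those sizes.

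**4. If progression is more variable than planned (assumption).** Lognormal data, one look at 4 per arm, simulated:

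| CV | Crosses, no effect | Of those, Welch p ≥ 0.05 | Crosses, true 50% effect |
|---|---|---|---|
| 100% | 1.6% | 91% | 14% |
| 150% | 5.7% | 95% | 21% |
| 200% | 9.2% | 96% | 25% |

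At 3 per arm the no-effect figures are 2.9%, 8.0% and 11.8%. On the plan's own SDs, a true 50% effect crosses at 4 per arm in only 1.3% of trials; with the treated SD at 48,000 instead of 24,000, it is 11%.

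**5. How large must the SD be?** With normal data, one look exceeds a 2.5% no-effect crossing only once the SD passes about 63,000 (2 per arm), 77,000 (3) or 89,000 (4).

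**The case against.** A reader might infer that a handful of scans can end the randomised comparison on noise. The plan's own figures do not support that. At an SD of 48,000 the trigger is strict: it lies well above the 60,000 mm³ target, and a no-effect crossing at 3–4 per arm is below 0.1%. The larger rates need CVs of 100–200% against the planned 40%. The Discussion calls progression significantly heterogeneous but gives no figure.

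A reader might also infer that no valid 5% test remains. That is not supported either. On the plan's inputs, overall error reaches only 5.3% even with six looks. With one look and lognormal CV 100% it is 4.4% at 4 per arm, because the Welch test is conservative there. It exceeds 5% only at CV 100% with 3 per arm (5.7%) or at CV 150–200% (6–13%).

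Nor is the committee bound to stop. The wording is permissive, safety comes first and a statistician sits on the committee. The number and timing of looks may stand in the full protocol, an SAP or a charter, and their absence from an article is no fault.

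All of this limits the size of the point. What remains is that the article does state a criterion, and the criterion as stated can be met by data that would fail the trial's own primary test.

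**Conclusion.** The point holds in a limited form. The stated efficacy trigger has no error control built into it. On the planning SDs it would rarely mislead when the drug has no effect (0.08% at 3 per arm, 0.014% at 4), yet at 2–3 per arm it can be met with Welch p of 0.18 or 0.064. Its safety rests on the 40% CV holding and on looks not being taken very early or often. Under the assumed CVs of 100–200%, one look at 4 per arm gives 1.6–9% false crossings, nearly all non-significant. A true 50% effect would be announced as more than 75% in 14–25% of trials.

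These figures rest on reading efficacy as the reduction in mean change, on equal SDs under no effect, and on assumed interim sizes. The rule should be amended, but it does not invalidate the planned primary analysis.

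**What to change.** Define efficacy as the relative reduction in mean HO change, and state that an efficacy recommendation requires all of the following:

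- an observed reduction above 75%;
- a prespecified stringent significance boundary;
- one planned look, with a stated minimum number of month-6 CTs per arm;
- a named interim test that can reach the boundary at that size;
- a final alpha set accordingly.

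The fourth condition matters. A boundary of p < 0.001 with 10 scans, for example, could never be met by exact Mann-Whitney, whose minimum at 5 per arm is 0.0079. With Welch, normal data, the 40% CV in both arms and a true 90% reduction, that boundary together with the 75% criterion is met in only about 18% of trials. The operating characteristics of the chosen rule should therefore be reported.

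The alternative is to restrict the DSMB to safety and delete the efficacy trigger.

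The cost is wording in the protocol and the committee's charter. Final power need hardly move: an O'Brien-Fleming-type boundary at half information (about p < 0.003), leaving about 0.049 for the final test, takes it from 81.5% to 81.2% at 8 per arm. The downside is that an early efficacy stop becomes much less likely. That loss is small, because under Intervention, comparator and concomitant care every participant moves to active drug at month 6.

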### Statistical approach

#### Sample size calculations

Based on the Natural History Study of FOP, progression of HO in FOP is estimated at 120,000 mm^3^ on average per 6-month period with a standard deviation of 48,000 mm^3^ [24]. Expert consensus defines a meaningful decrease in the rate of HO progression as at least 50% reduction in treated vs. control patients, or 60,000 mm3, with a standard deviation of 24,000 mm^3^. Using this projected impact, using a t-test with two-sided alternative, with unequal variances, a trial with treatment and placebo arms of *n* = 8 each would be 80% powered to detect this minimum clinically meaningful difference with an α = 0.05 during the initial 6-month study.

Taking into account an expected drop-out rate of 20%, we calculated the necessary number of participants to be 20 at the start of the study.

